#### Possible confounders and mediators

Participants will self-report age, sex, education status, stress level, work status and medication use, diet, alcohol consumption, smoking, feeling of satiety, and satiation. Autonomous nervous system activity will be assessed using an electrochemical skin conductance test, and cardiovascular health will be assessed using a standard resting 12-lead ECG and coded according to the Minnesota coding system. Sleep rhythms, quality, and sleep phases will be assessed using at-home EEG measurements using the ZMax headband [18], accelerometers (ActiGraph), sleep diaries, and the MCTQ questionnaire. Additionally, Dim Light Melatonin Onset was assessed using 6-point saliva measurements and 3-point saliva measurements for cortisol awakening reaction (in a subgroup) and physical activity (total activity levels, moderate to vigorous physical activity, and total sedentary time) measured using an accelerometer.

### Participant timeline {13}

Figures 1 and 2 present a timeline of the enrollment, study visits, intervention period, and measurements taken. Participants are invited to the research center in the afternoon and informed consent is signed. Then participants will go home and will fill out VAS scales about satiety and satiation before and after having dinner. A subgroup (*n* = 15) will be asked to wear light-dimming goggles for one evening and collect six saliva samples for melatonin onset assessment. After that, all participants will wear an activity tracker (ActiGraph) at home during regular activities and a sleep monitoring headband (ZMax) at night for a period of 6 days and they will fill in a sleep diary during this period. During the second study day at baseline, anthropometrics and blood pressure will be measured and blood will be drawn to determine HbA1c levels as well as fasting insulin and glucose levels. Participants will also fill in a VAS scale on satiety and satiation and several questionnaires. After that, an ECG and electrochemical skin conductance test will be performed. At the end of the visit and after the participants receive breakfast, they will be randomly assigned to either the control or intervention group and they will receive information on the intervention program or control condition.

**Fig. 1 Fig1:**
[figure not shown]
Timeline of study visits, intervention, and measurements of the social jetlag trial

**Fig. 2 Fig2:**
[figure not shown]
Schedule of enrolment, interventions, and assessments social jetlag trial

To improve adherence to the protocol and assess compliance, 1 week after starting the intervention, participants will keep a sleep diary of 7 days and wear an accelerometer as well as a light tracker.

After a period of 3 weeks, all participants will wear an activity tracker and a sleep-monitoring headband for 5 days and fill in a sleep diary. After that, participants will be invited back to the research center once for the same measurements as the second day of the baseline visit (anthropometrics, blood pressure, blood draw, ECG and SUDO, and questionnaires). Twelve weeks after the start of the intervention, they will wear an activity tracker for 5 days again and they will come back to the research center for a final visit repeating the same measurements.

### Sample size {14}

We calculated the sample size based on the primary outcome, namely HbA1c after 12 weeks. To date, no previous study investigating these social jetlag-reducing interventions has assessed metabolic outcomes. Previous lifestyle interventions in the target population show a change in HbA1c over a period of 3–6 months of 0.2–0.75% [19, 20]. We hypothesize a difference of − 0.25% in HbA1c levels between the two groups after the current intervention. To assess a change of − 0.25% ± 0.25 in HbA1c level, with an *α* of 0.05 and *β* of 0.1 the (corrected) number of participants needed is 23 persons per group, with an anticipated 25% drop-out, this results in 30 participants per group [19, 20].

### Recruitment {15}

Participants from our cohorts, who gave consent for future research and who are eligible for this study will be invited. Eligible people will receive detailed written information. They will receive an invitation letter together with the participant information. After 2 weeks, participants will be contacted by telephone by the researcher to discuss participation and plan the study visit. Before the start of the first measurements, the researcher will discuss the study procedures: the purpose, nature, and duration of the research and the related risks and benefits, as well as the consent. The researcher will answer all questions and obtain a written informed consent before the start of the study. This informed consent form will have to be signed at the research center in the presence of one of the investigators or research nurses. Before signing of the informed consent, no measurements will be performed and no invasive questions will be asked.

### Assignment of interventions: allocation

#### Sequence generation {16a}

Randomization will be performed automatically by the Electronic Data Capturing software (Castor EDC) [21]. Blocked randomization will be used to ensure a good balance of participant characteristics in each group. As sex and age have a strong influence on sleep behavior and also on metabolic and glycemic parameters, randomization will be stratified on sex, two strata of age, and two strata of social jetlag (based on levels in our source population) to prevent imbalance. Allocation will be determined by using a computerized random number generation process.

#### Concealment mechanism {16b}

Not applicable.

#### Implementation {16c}

After the baseline measurements are finished on study day 2, participants will be notified whether they are randomized to the intervention or control condition. Participants in the control condition will receive advice on sleep hygiene but are not instructed to change their sleeping conditions and habits. The participants in the intervention group will receive instructions and all materials needed to follow the intervention protocol. They will also receive materials and instructions for the compliance measurements that they will conduct independently from home.

### Assignment of interventions: blinding

#### Who will be blinded? {17a}

Blinding of the research team and participants to treatment allocation is not possible due to the nature of the intervention. Statistical analyses will be performed by a blinded independent researcher.

#### Procedure for unblinding if needed {17b}

Not applicable because the research team and participants are not blinded.

## Data collection and management

### Plans for assessment and collection of outcomes {18a}

HbA1c will be determined from a fasting blood sample after 12 weeks as a measure for long-term glucose control. All data collected during the study visits will be entered into the eCRF (Castor EDC) directly afterwards. Lab results will be entered in the eCRF as soon as they are determined by the laboratory. Finally, the questionnaires will partly be filled in by the participants using Castor EDC and will partly be on paper and subsequently entered in Castor EDC by the research team.

### Plans to promote participant retention and complete follow-up {18b}

As we will recruit participants from our existing study cohorts, they will already be familiar with participating in scientific research. To promote participant retention and follow-up, participants receive written appointment confirmations at home.

### Data management {19}

We will use Castor EDC as a clinical data management system to capture all collected data in electronic case report forms (eCRF) [21]. Data validation checks and notifications are embedded in the eCRF to ensure correct data entry. All original study documents will be filed in the Trial Master File (TMF) and Investigator Site File (ISF).

### Confidentiality {27}

The handling of personal data complies with the Dutch Personal Data Protection Act (AVG/GDPR). The data of all participants that will participate in the present study will be coded. All participants have an identification number, consisting of four numbers, obtained during previous studies. These numbers cannot be traced to the person without the key, which is stored separately. The key document is only available to the participating investigators. Participants can request the information stored in their CRF.

### Plans for collection, laboratory evaluation, and storage of biological specimens for genetic or molecular analysis in this trial/future use {33}

All biological samples collected during this study will be analyzed during or at the end of the study. All remaining materials will be destroyed afterwards.

## Statistical methods

### Statistical methods for primary and secondary outcomes {20a}f

Baseline characteristics will be described by the intervention arm as mean ± standard deviation (SD), as the median and interquartile range (if not normally distributed), or as numbers and percentages if categorical. Statistical analysis will be performed using RStudio version 4.3.0. We will conduct intention-to-treat analysis for primary and secondary outcomes using linear regression analysis, adjusting for baseline values. We will also adjust for the use of diabetes medication and perform sensitivity analyses on changes of medication use during the follow-up period of the study. Additionally, we will assess differences in intervention compliance and effect according to seasonality. Not normally distributed outcomes will be log transformed. We will assess effect modification by working status and chronotype. We will consider the chance of false positive findings when interpreting the results from testing our multiple secondary outcomes. If there is (despite randomization) an imbalance in participant characteristics, a sensitivity analysis will be conducted to assess the effect of the imbalance by adjusting for these variables.

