## Introduction

### Background and rationale {6a}

Social jetlag is a chronic disruption of sleep timing. It is caused by a discrepancy between biological rhythms and social engagements and is characterized by different sleep timing during workdays and free days [1]. Unlike sleep disruption caused by performing shift work or by traveling through different time zones, social jetlag is subtle but highly prevalent with estimates of over 70% in students and over 50% in the working population [2, 3]. Social jetlag usually starts during adolescence and remains present throughout the working career [1–4].

Social jetlag is associated with several pathologies such as mental health, cardiovascular disease, and type 2 diabetes [2]. In our recent meta-analysis, with data from 68 studies, we found that social jetlag is significantly associated with higher HbA1c levels, higher odds of obesity, and increased BMI [5]. In our cross-sectional study in people with type 2 diabetes, we showed that in working people, a high social jetlag was associated with a 1.87 mmol/mol (95% CI: 0.75 to 2.99) higher HbA1c and 5.81 mmHg (95% CI: 4.04 to 7.59) [6] higher blood pressure.

In other words, social jetlag can contribute to poorer glycemic and metabolic control in those with type 2 diabetes. As type 2 diabetes is a highly prevalent disease that causes a high burden of disease with over 400 million people affected worldwide [7], reducing social jetlag could offer a way to reduce this disease burden and improve overall population health.

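### The primary HbA1c model leaves out the three factors by which randomisation is stratified; to the extent that they are prognostic, the test is conservative and some precision is lost

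*Protocol article*

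**What the plan says.** The protocol article's section on sequence generation (16a) states that "randomization will be stratified on sex, two strata of age, and two strata of social jetlag", using blocks. It gives a prognostic reason: "As sex and age have a strong influence on sleep behavior and also on metabolic and glycemic parameters". The trial design section (8) names the same three factors.

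The section on statistical methods (20a) fixes the model for primary and secondary outcomes as an intention-to-treat analysis with two kinds of adjustment: "using linear regression analysis, adjusting for baseline values. We will also adjust for the use of diabetes medication". Neither sex, age nor social jetlag is listed. Other characteristics can enter only conditionally: "If there is (despite randomization) an imbalance in participant characteristics, a sensitivity analysis will be conducted".

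**The concern.** Blocking within strata makes the arms alike on the stratification factors. Where those factors are prognostic, the true sampling variance of the treatment difference falls. A model without them still counts their contribution as residual noise. Its standard error then overstates the real uncertainty, the confidence interval is wider than it needs to be, and the test rejects less often than its nominal 5% under the null.

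The imbalance rule does not close the gap. Stratification makes imbalance on these three factors unlikely, so the rule would seldom be triggered for them. If it were, it would add only a sensitivity analysis and leave the primary result as it is. At stake is efficiency in a trial planned on 23 evaluable people per arm, not validity.

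**Working it through.** **1. The plan's own figure.** Inputs from the sample size section (14): difference 0.25% HbA1c, SD 0.25%, α 0.05, β 0.1. The standardised effect is 0.25/0.25 = 1.0.

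- Normal approximation, two-sided: n = 2(1.960 + 1.282)² × (0.25/0.25)² = 21.0, so 22 per group.
- t-test: 22 per group gives 89.97% power and 23 gives 91.2%, so 23, as stated.
- Drop-out: 22/0.75 = 29.3, so 30; 23/0.75 = 30.7, so 31. The stated 30 fits within rounding.

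The starting point is therefore 46 evaluable people and about 91% power.

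**2. The mechanism.** Let R2 be the share of the 12-week HbA1c variance remaining after baseline HbA1c that the three factors explain. With perfect balance on the factors, the true standard error is √(1 − R2) times the one the reduced model reports. The actual two-sided type I error is then P(|Z| > 1.96/√(1 − R2)):

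- R2 = 0.05: 1.96/0.975 = 2.01, giving 4.4%
- R2 = 0.10: 1.96/0.949 = 2.07, giving 3.9%
- R2 = 0.20: 1.96/0.894 = 2.19, giving 2.8%
- R2 = 0.30: 1.96/0.837 = 2.34, giving 1.9%

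Real blocks leave some imbalance, so the actual values should lie nearer 5%.

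**3. Simulation.** 10,000 trials per scenario, 46 evaluable people, 2 × 2 × 2 = 8 strata and permuted blocks of 4 (assumed; the article gives no block size). The outcome is regressed on arm and baseline HbA1c, without and with the three factors. The standardised effect is 1.0 for power and 0 for type I error. The documents give no R2, so a range is shown. Standard errors are in residual-SD units and refer to the model without the factors.

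| Assumed R2 | Mean model SE | True SD of estimate | Type I error, omitted / included | Power, omitted / included | Power lost (points) |
|---|---|---|---|---|---|
| 0 | 0.297 | 0.295 | 4.7% / 4.7% | 90.7% / 90.1% | −0.5 |
| 0.05 | 0.297 | 0.291 | 4.3% / 4.9% | 91.5% / 92.0% | 0.6 |
| 0.10 | 0.298 | 0.289 | 4.3% / 5.4% | 91.6% / 92.9% | 1.3 |
| 0.20 | 0.297 | 0.274 | 3.2% / 5.0% | 92.3% / 95.3% | 2.9 |
| 0.30 | 0.298 | 0.257 | 2.5% / 4.7% | 93.4% / 97.3% | 3.9 |

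The Monte Carlo error of each type I error is √(0.05 × 0.95/10,000), about 0.2 points. Losses are taken from unrounded power.

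At R2 = 0.20 the reported standard error is 0.297/0.274 = 1.08 times the true one; at 0.10 it is 0.298/0.289 = 1.03 times. Blocks of 8 instead of 4, or drop-out applied after randomisation, shift these figures a little but do not remove the effect. The ranges in the verdict allow for that spread.

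**4. Which R2 is plausible?** The only figure in the article is cross-sectional, in working people with type 2 diabetes: "a high social jetlag was associated with a 1.87 mmol/mol (95% CI: 0.75 to 2.99) higher HbA1c". Assumptions: 1 mmol/mol is 0.0915% HbA1c, two equal strata, residual SD 0.25%, a slope on baseline HbA1c of 0.7 to 0.9, and a factor that acts only through the HbA1c level.

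- Crude difference: 1.87 × 0.0915 = 0.171%.
- Left after baseline adjustment: 0.171 × (1 − 0.7) = 0.051%, down to 0.171 × (1 − 0.9) = 0.017%.
- R2 of this one factor: (0.051/2)²/0.25² = about 1%, down to (0.017/2)²/0.25² = about 0.1%.

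For three equal factors to reach a joint R2 of 0.10, each must leave a difference of 2 × 0.25 × √(0.10/3) = 0.091%. At slopes of 0.7 to 0.8 that is a crude difference of 0.091/0.3 = 0.30% to 0.091/0.2 = 0.46%, or 3.3 to 5.0 mmol/mol. A joint R2 of 0.30 needs 5.8 to 8.6 mmol/mol per factor.

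**The case against.** The strongest counter-argument is that baseline HbA1c is already in the model. Sex and age are stable over 12 weeks, so much of their influence on HbA1c is carried by the baseline value, and medication may carry more. The stated rationale concerns glycemic parameters in general, not what remains after that adjustment. Step 4 shows that the one quantified association leaves an R2 of about 1% or less if it acts only through the level. This stands. It makes the concern conditional and makes the lower end of the range the better supported one. It does not remove the concern, because a factor may also predict change directly and the documents do not settle this either way.

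The simulation also omits medication and assumes the block size. Both points are fair, although blocks of 8 do not remove the effect.

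A fuller analysis plan might add the factors. However, the article is not silent on covariates: it names them, and these three are not among them.

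A reader might infer that the analysis is invalid, that the trial is underpowered, or that all the precision gained by stratifying is wasted. The documents do not support any of these. The estimate is unbiased, the error in the test is on the safe side, and power of the model without the factors itself rises from 90.7% to 93.4% over the range of R2, so part of the gain is kept. Nor is the imbalance-triggered adjustment an error that must be deleted: it is labelled a sensitivity analysis and cannot change the primary result.

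**Conclusion.** The concern holds as a conditional efficiency point. The primary model omits the factors used to stratify randomisation. To the extent that they predict 12-week HbA1c beyond baseline HbA1c and medication, its standard error is too large and its test conservative.

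- **Assumed R2 of 0.05 to 0.10:** type I error about 4.0 to 4.5%, and about 0 to 1.5 points of power lost.
- **Assumed R2 of 0.20 to 0.30:** type I error about 2.5 to 3.7%, and about 3 to 6 points lost. The documents do not support this range directly.

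The loss is relative to the adjusted model, not to the planned target; under the plan's own effect and SD, power stays at about 90% or more. These sizes rest on the assumed R2 and block sizes, 46 evaluable people, and reading the baseline adjustment as the baseline value of the outcome.

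**What to change.** In the section on statistical methods (20a), pre-specify sex, age and baseline social jetlag as fixed covariates in the primary and secondary regression models, alongside the baseline outcome value and diabetes medication. State now whether age and social jetlag enter as randomised (two strata each) or as continuous values. Where social jetlag is itself the outcome, its baseline value may already serve as that covariate.

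The imbalance-triggered sensitivity analysis may stay for other variables.

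The cost is one sentence and three degrees of freedom, which is under one point of power if the factors explain nothing (90.7% against 90.1% in the simulation). No new data are needed, since the factors must be known at randomisation. The article reports the trial as ongoing, so the change can be fixed before the outcome data are analysed.

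### The covariate sensitivity analysis is triggered by, and built from, chance baseline imbalance rather than from variables expected to predict 12-week HbA1c

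*Protocol article*

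**What the plan says.** In the protocol article, the section on statistical methods for primary and secondary outcomes {20a} sets an intention-to-treat comparison "using linear regression analysis, adjusting for baseline values", and adds "We will also adjust for the use of diabetes medication". It closes with a conditional step: "If there is (despite randomization) an imbalance in participant characteristics, a sensitivity analysis will be conducted". The stated aim of that step is "to assess the effect of the imbalance by adjusting for these variables". One observation, the difference between the arms at baseline, therefore decides both whether the analysis is done and which covariates enter it. The section gives no measure of imbalance, no threshold and no list of characteristics.

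The section on sequence generation {16a} states that "randomization will be stratified on sex, two strata of age, and two strata of social jetlag", and gives the reason for the first two factors: "As sex and age have a strong influence on sleep behavior and also on metabolic and glycemic parameters". Section {20a} does not name these three factors as covariates. The pool from which imbalanced variables could come is wide. The section on possible confounders and mediators says "Participants will self-report age, sex, education status, stress level, work status and medication use, diet, alcohol consumption, smoking, feeling of satiety, and satiation", and baseline clinical, sleep and activity measures come on top of that.

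**The concern.** If allocation is properly random, every baseline difference is a chance difference. Adjusting for a covariate helps the HbA1c comparison to the extent that the covariate predicts HbA1c; whether the arms happen to differ on it is a separate matter. A rule driven by observed difference will admit variables that differ but do not predict the outcome, and omit variables that predict it but look balanced. Stratification makes the second error likely for sex and age, the factors the article itself singles out.

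At stake is the reading of the robustness check. It is the only stated check on baseline covariates beyond those in the main model: the other planned checks concern medication changes during follow-up, seasonality and adherence. If its covariates are set by chance and its standard error is larger than necessary, a sound result can look fragile, or a fragile one sound. A later definition of imbalance would settle when the check runs, but it would not make imbalance a sensible basis for choosing covariates.

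**Working it through.** **Inputs.** The sample size section {14} gives a difference and SD through "To assess a change of − 0.25% ± 0.25 in HbA1c level", with α 0.05, β 0.1, 23 evaluable and 30 randomised per group. Assumed: two-sided testing, 5 to 20 candidate characteristics (12 in the simulation), independent normal covariates, and the share of residual variance that prognostic covariates explain (R²).

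**The plan's own figure.** n = 2(1.960 + 1.282)² × (0.25/0.25)² = 21.0, so 22 per group; the t-based version gives 23, as stated. Dividing 23 by 0.75 gives 30.7 and 22 by 0.75 gives 29.3, so the stated 30 is reproduced to within one person per group. I use 30.

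**How often the check would run.** The SE of a standardised mean difference (SMD) is √(2/30) = 0.258. The chance that one characteristic is flagged is p = 2[1 − Φ(c/0.258)] for an SMD cut-off c, or the significance level for a test. The chance that at least one of K is flagged is 1 − (1 − p)^K.

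| Criterion | p | K = 5 | K = 12 | K = 20 |
|---|---|---|---|---|
| p<0.05 | 0.050 | 23% | 46% | 64% |
| p<0.10 | 0.100 | 41% | 72% | 88% |
| SMD>0.5 | 0.053 | 24% | 48% | 66% |
| SMD>0.25 | 0.333 | 87% | 99% | 100% |
| SMD>0.2 | 0.439 | 94% | 99.9% | 100% |

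For example, 1 − 0.95¹² = 0.46 and 1 − 0.667¹² = 0.99. Correlated characteristics would lower these figures somewhat.

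**What the check selects.** In 3,000 simulated trials per setting, with 12 candidates of which 3 were prognostic, the rule flagged about 0.6 variables under p<0.05 and about 5.3 under SMD>0.2. About 25% of the flagged variables were prognostic. That is 3/12, their share of the pool, so the trigger does not favour useful covariates.

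**Precision.** Mean SE of the treatment effect, 30 per arm, residual SD 1 after baseline adjustment:

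| R² | Trigger | Triggered | Fixed set of 3 | Baseline only | Triggered vs fixed |
|---|---|---|---|---|---|
| 0 | p<0.05 | 0.2677 | 0.2671 | 0.2598 | about 0% |
| 0 | SMD>0.2 | 0.2853 | 0.2666 | 0.2594 | +7% |
| 0.10 | p<0.05 | 0.2670 | 0.2531 | 0.2598 | +5% |
| 0.10 | SMD>0.2 | 0.2800 | 0.2529 | 0.2596 | +11% |
| 0.25 | p<0.05 | 0.2658 | 0.2308 | 0.2595 | +15% |
| 0.25 | SMD>0.2 | 0.2691 | 0.2302 | 0.2590 | +17% |

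The estimated SE of the triggered model exceeds that of the baseline-only model in every row. The actual spread of the estimates tells a slightly milder story. In the four rows with R² above 0 it is 5% to 12% larger than with the fixed set, and at R² = 0.25 it is about the same as with baseline only (0.2638 vs 0.2661; 0.2563 vs 0.2581). At R² = 0 no adjustment helps; the +7% arises because the trigger admits more than five useless covariates against three.

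**Type I error and power.** The triggered test rejected in about 4% to 6% of null trials. At the plan's effect, 0.25/0.25 = 1.0 SD, and the most adverse row, the effect is 1/0.2691 = 3.72 SEs triggered and 1/0.2302 = 4.34 fixed. With a critical value near 2.00, power is about Φ(1.72) = 96% against Φ(2.34) = 99%.

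**The case against.** The strongest reply is that the sentence governs a labelled sensitivity analysis and has its own purpose: to ask whether a visible imbalance explains the result, not to maximise precision. A fixed list cannot answer that for a variable that is not on it. The main model is specified without reference to balance, and the article assigns the analysis to a blinded independent researcher, which limits deliberate steering. The definition of imbalance may also sit in a fuller plan.

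Much of this stands. The missing definition is not the finding, and blinding does guard against steering, though not against chance selection. The question about a striking imbalance is legitimate, but an imbalance distorts the comparison only if the variable predicts HbA1c. A set chosen for prognosis covers the foreseeable cases, and the rest can be explored under that label.

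Three stronger readings are tempting and are not supported:

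- **That the check would nearly always run.** This holds only for a low SMD cut-off, about 0.25 or less. Under p<0.05 with 5 to 12 characteristics it runs in fewer than half of trials, and the article does not say which criterion applies.
- **That the primary result is biased or its error rate inflated.** The rule does not touch the primary model, and the simulated rejection rate stays near 5%.
- **That much power is lost.** At the plan's own effect of 1.0 SD the difference is about 96% against 99%, in a secondary analysis, under the most favourable R² assumed for the fixed set.

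**Conclusion.** The point holds as a matter of analysis choice. The stated rule ties the covariate check to a quantity unrelated to prognosis and tends to skip factors the article itself regards as influential. The cost is a less precise robustness check with contents determined by chance. The SE is about 5% to 17% larger than with a fixed set that explains 10% to 25% of residual variance, and there is little or no difference if that set is not prognostic. These R² values, the 12 candidates and their independence are assumptions, and stratification was not simulated. The conclusion about selection does not depend on them; the percentages do. Nothing here threatens the primary inference, so this is a cheap improvement rather than a necessary correction.

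**What to change.** Replace the imbalance trigger in section {20a}. Before data lock, name a short covariate set chosen for expected association with 12-week HbA1c. It should contain the stratification factors (sex, age and social jetlag) and, for example, baseline BMI. Fit the main model with these added whatever the observed balance, and report the estimate and interval beside the primary one. If a striking imbalance appears in a variable outside the set, a further adjustment may be shown, labelled exploratory.

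The change is a sentence or two of analysis wording and uses variables already planned for baseline. The downside is a few degrees of freedom in a sensitivity analysis. In the simulation, three covariates with no prognostic value raised the mean SE from 0.2598 to 0.2671, or about 3%.
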